## Abstract

Despite the increasing importance of innovative medications and bariatric surgery for the treatment of obesity, lifestyle interventions (diet and physical activity) remain the first-line therapy for this disease. The use of digital devices in healthcare aims to respond to the patient's needs, in order to make obesity treatment more accessible, so our study aims to assess the safety and efficacy of a Digital Therapy for Obesity App (DTxO) for achieving weight loss and its maintenance in patients affected with obesity undergoing an experimental non-pharmacological treatment. Here we present the study protocol of a prospective, multicenter, pragmatic, randomized, double-arm, placebo-controlled, parallel, single-blind study on obese patients who will be treated with a new digital therapy to obtain an improvement in their disease condition through the application of different simultaneous strategies (a dietary regimen and personalized advice program, a tailored physical exercise program, a cognitive–behavioural assessment and program, alerts and reminders, dedicated section on prescribed drugs intake, and chat and online visits with clinical professionals). We believe that DTxO will offer a promising intervention channel and self-regulation tool holding the potentiality to decrease treatment burden and treat more patients thanks to the partial replacement of traditional medical consultation with digital or telephone management, improving self- engagement and reducing the high demands the “obesity pandemic” for both patients and national health services in terms of time, cost, and effort.

**Clinical trial registration**: clinicaltrials.gov, identifier, NCT05394779.

## Introduction

1.

Obesity is defined as a multifactorial disease characterized by an excess of body fat which is associated with a significantly higher risk of multiple chronic diseases, for example diabetes mellitus, cardiovascular disease (CVD), depressive disorder, and different types of neoplasia (1–3). Moreover, obesity is associated with significant impairments in patients’ quality of life and even a reduction of life expectancy ranging from 5 to 20 years (4, 5).

Its prevalence has been globally increasing in the last 50 years to the extent that it is nowadays defined as an “obesity pandemic”, with the Global Burden of Disease (GDB) recently reporting that almost one third of world population can be listed as overweight or obese (5). Also in Italy obesity prevalence is rising, increasing by almost 30% in adult population in the last 30 years (6). Despite the increasing employment of medications and bariatric surgery for the treatment of obesity (7), lifestyle interventions (hypocaloric diet, physical activity, and cognitive-behavioral therapy) remain the first-line treatment (8). However, long term weight loss maintenance can be difficult both for metabolic readjustment and for the arduousness in lifestyle changes compliance, and patients often suffer weight regain following initial weight loss (9–11). Moreover, although drastic lifestyle changes usually lead to clinically significant and durable weight loss, they often require multiple in-person sessions with high demands for patients and national health services in terms of time, cost, and effort (12). Therefore, behavioral weight loss still has the unsolved issue of how to reduce healthcare intensity not affecting the regular social support, reliability, and feedback essentials to improve and preserve the “patient empowerment”. This recent concept has been proposed for managing diabetes (13) and is based on the concept that the patient is more encouraged to follow self-chosen behavioral adjustments than changes prescribed by others. Self-education with extensive lifestyle modifications and systematic self-monitoring provides positive and long-term effects on metabolic profile, together with quality of life, knowledge, and healthy behavior improvements (14).

It is in this context that digital health tries to respond to the patient's needs and makes the management of this condition more accessible (15). Scientific research has investigated different options of weight loss programs (computer, TV programs, smartphone applications), in order to meet patient's necessities and make obesity treatment more available (15). Smartphones indeed can be a valid option becoming a self-education device holding the capacity to reduce healthcare's workload and treat more people through the partial replacement of traditional medical consultation with digital or telephone management (16, 17). This approach seems the most convenient and accessible, considering the widespread use of smartphones among the population and the fact that weight-loss apps (Apps) can help reinforce dietary plan compliance, physical activity, and weight monitoring with the expedient of progress awareness through goals' achievement (18, 19). Consistent with these findings, our study aims to assess the safety and performance of a Digital Therapy for Obesity App (DTxO) for weight loss and its maintenance in patients affected with obesity undergoing an experimental non-pharmacological treatment. The primary objective is to evaluate the weight loss in patients using DTXO compared to control patients (Placebo App patients DTXO after a period of 6 and 12 months of DTXO use. The secondary objectives are:
1.To assess the degree of dietary recommendation adherence (Mediterranean dietary pattern questionnaire) and of improvement of food and nutrition knowledge (Food Knowledge Moynihan Questionnaire) of the two groups during our study2.To evaluate the reduction of physical inactivity (reduction) (IPAQ Questionnaire), lower limbs physical function improvements (SPPB test) randomized in the two randomized group.3.To measure the reduction of stress (DASS-21 scale), the increase in goodwill to approach therapy (URICA-28 scale), the increase in the (various) self-esteem in coping with life's challenges (GSES-10), the measure of Binge Eating Behaviour (BES-16 scale), the measure of emotion regulation problem (DERS-36 scale), the increase of quality of life (PGWBI questionnaire), the measure of sleep habits (PSQI) in each randomized group4.To identify the level of acceptability in the use of DTxO after 12 months

## Material and methods

2.

### Study design

2.1.

This is a prospective, multicenter, pragmatic, randomized, double-arm, placebo-controlled, parallel, single-blind study on obese patients treated with a new digital therapy (DTX Obesity) to obtain an improvement in their disease condition through the application of different simultaneous strategies (a dietary regimen and personalized advice program, a tailored physical exercise schedule, a cognitive-behavioural assessment and program, alerts and reminders, dedicated section on prescribed drugs intake, and chat and online visits with clinical professionals) (see Figure 1).

**Figure 1 F1:**
[figure not shown]
Study design of the DEMETRA study.

### Study setting

2.2.

The clinical centers involved in the trial are Istituto Auxologico Italiano and Azienda Ospedaliero-Universitaria Consorziale Policlinico Di Bari, specialized centers in obesity care. Both centers fully take part in trial activities, in the enrolling and take in charge of participants, implementation of interventions, and assessment of results. Heterogeneity is guaranteed both by the high number of patients, all enrolled in a comprehensive obesity outpatient clinic, and by the fact that the two centers are respectively in North and South of Italy, areas with different lifestyle and food habits.

### Study duration

2.3.

The estimated study duration is 16 months. Recruitment will last approximately 4 months. Each patient will be followed for approximately 12 months after the baseline visit.

### Eligibility criteria

2.4.

#### Inclusion criteria

2.4.1.

•Participants must be between 18 and 65 years of age at the time of informed consent.•Informed consent form (Capability of giving informed consent, including compliance to requirements and restrictions listed in).•BMI between 30.0 kg/m2 and 45 kg/m2.•Participants must own, be prone to use technology of mobile Apps (tech-savvy) and be able to download the App described in the protocol.•Italian language native speakers or foreign patients who fully understand Italian language, as the information and instructions for health programs will be in Italian.

#### Exclusion criteria

2.4.2.

•Diseases: recent cardiovascular event (<6 months), heart failure (class >II), GFR <60 ml/min, type 1 diabetes, cancer within the first 5 years; drug or alcohol abuse, active eating disorder or history of bulimia and anorexia nervosa, Binge Eating Scale score >27, psychiatric disorders not compensated, score ≥2 in the “Depression,” “Anxiety” and “Psychoticism” subscales of the Symptom Checklist-90-R; visual or vision impairments; secondary obesity, Edmonton Obesity Staging System score >4; bariatric surgery in the previous 2 years; referred pain to lower limb joints on the Numeric Rating Scale ≥5; recent (<6 months) weight loss ≥10%.•Prior/Concomitant Therapies and other exclusions: Changed in pharmacological therapy with drugs that may affect eating behavior and/or energy metabolism during the last 3–6 months; participation in other weight-loss programs or in other clinical trials; known child-bearing women; any condition could the results of the study. Potentially interfering with the results of the study according to the investigator.

The presence of inclusion criteria and absence of exclusion criteria is investigated during the visit.

### Recruitment

2.5.

This study will include consecutive obese adult patients who self-referred to obesity centers seeking weight-loss treatment at the centers involved in the trial: patient enrolment will occur during a visit with an endocrinologist and a dietitian. Before any screening procedure, all patients must sign a written informed consent for the study.

### Training

2.6.

The training and experience necessary to use the device subject to pre-market clinical investigation (a device with pending CE marking and used in the investigation according to its intended use) were evaluated during the risk assessment of the device. It has been shown that the provision of information for safe use (User Manual) is sufficient for the healthcare professional user. Additionally, specific onboarding procedures for the patient have been determined as per the onboarding experience. Users will also be instructed to report any software malfunctions to the assistance service by emailing a dedicated assistance portal.

### Randomization

2.7.

Patients will be randomly assigned 1:1 to the intervention or comparison group according to a pre- defined, centralized randomization list. Randomization is indeed globally guaranteed between the two centers. To maintain an overall balancing between groups, we will perform block randomization (using random block sizes of 8 patients) (“plan”).

### Blinding and unblinding procedures

2.8.

Patients in the control arm will be provided with a placebo App to maintain patients' blindness to treatment allocation. Breaking the blind during the study (for a single subject) should be considered only when knowledge of the treatment assignment is deemed essential by the investigator due to immediate safety concerns or is considered essential for the immediate management of the subject, and should be discussed with the sponsor beforehand, if possible. It is the responsibility of the investigator to promptly document and explain any unblinding to the sponsor. Any unblinding will result in the discontinuation of subject participation from the study.

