### Study intervention

2.9.

DTxO is an investigational therapeutic intervention for obese patients, under clinical validation with a randomized and placebo-controlled clinical trial for confirmatory purposes. DTxO is downloadable software for mobile devices (smartphone, tablet), classified as Class IIa Medical Device (MD), available for patients as an application (App) that integrates different non-pharmacological approaches. It is intended to improve weight loss, weight-loss maintenance, and overall health in patients with obesity by increasing their self-engagement, self-monitoring and adherence to dietary/exercise and behavioral programs. The App integrates different non-pharmacological approaches, engaging the patient through monitoring of her/his/them non-vital parameters, monitoring of patient diet and exercise, monitoring of patient psychological status, prescription of exercise and diet in a weight-loss program, and configurable data presentation charts for provision of additional information to professional users.

The Investigational Medical Device (IMD) consists of a Medical Web Application, also called Medical Dashboard, integrated into the electronic Case Report Form (eCRF), where the physician will collect patient's data necessary for enrolment and profile creation; and a Patient App, which will allow interacting with the patient to guide their behaviors, record therapeutic outcomes and improve therapeutic adherence.

The DTxO App will provide a dietary regimen with a personalized advice program, a tailored physical exercise program, a cognitive–behavioural assessment and support program, alerts and reminders, dedicated section on prescribed drugs intake and dietary and exercise program, chat and online visits with clinical professionals, and trophies to improve patient engagement. All these tools aim not only to weight loss, but they also help patients to improve their health and ameliorate their lifestyle.

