#### Baseline visit (V0)

2.10.1.

During the first visit, the patient will sign the informed consent form and will be evaluated for inclusion/exclusion criteria. Once the enrolment is confirmed, the patient is randomized 1:1 to either the experimental arm (DTx Obesity App) or control arm. The physician will explain to the patient how to download, access, and use the assigned App.

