#### Follow-up visit

2.10.2.

After the baseline visit, the patient will follow the dietary, physical and psycho- behavioural programs suggested by the physician and will use the DTXO/placebo App as explained by the physician. Face-to-face follow-up visits are foreseen at 3 months (V1), 6 months (V2), 9 months (V3) and 12 months (V4) after enrolment. During each visit, the following assessments are performed:
•Physical examination•Assessment of vital signs•Laboratory blood tests•Short Physical Performance Battery•Assessment of patient's responses to psycho-behavioural questionnaires by a psychologist. If any psycho-pathological problem is detected, the patient is referred to a specialist and exits the study.•Recording of concomitant medications•Safety assessment (adverse events investigation)

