### Study control

2.11.

The efficacy of the DTXO App will be assessed with the comparison of results with a group of patients treated with a standard of care approach (paper-based, in-person) and a placebo App.

The placebo App will include only the non-medical modules of the digital therapy, for example, patient onboarding data and access, while it will not include any medical module; for example, the digital placebo App will not allow the input of the patient's reported clinical data nor provide indications or reminders about the therapy or diagnosis.

The placebo App has been introduced to make the experience of subjects in the control arm more similar to that of subjects in the experimental arm; moreover, data collection through the placebo app (questionnaires) will streamline the data collection process, avoiding manual data entry and reducing the possibility of entry errors. Through the placebo App, the patient will be asked to complete weekly the Diet Adherence questionnaire (NRS scale). No trend graph will be provided to the patient to monitor their performance, nor any personalized content will be displayed. standard clinical practice. The placebo App will be used only as a data entry tool for questionnaires.

Patients in the control group will be provided with a dietary plan and nutritional education and behavioral contents in paper format.

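### Two post-randomisation rules end study participation, and so later outcome collection, where stopping blinded treatment or referring the patient would not require it

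*Protocol article*

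**What the plan says.** Section 2.10.2 (Follow-up visit) schedules face-to-face visits at 3, 6, 9 and 12 months (V1 to V4). One item at each visit is "Assessment of patient's responses to psycho-behavioural questionnaires by a psychologist". The rule attached to it is: "If any psycho-pathological problem is detected, the patient is referred to a specialist and exits the study".

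Section 2.8 (Blinding and unblinding procedures) lets the investigator break the blind for a single subject only when knowing the assignment is needed "due to immediate safety concerns or is considered essential for the immediate management of the subject". The investigator must document and explain this to the sponsor. The section ends: "Any unblinding will result in the discontinuation of subject participation from the study".

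Three other statements bear on the point:

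- The Introduction makes psychological scales secondary objectives, starting with "To measure the reduction of stress (DASS-21 scale" and going on to URICA-28, GSES-10, BES-16, DERS-36, PGWBI and PSQI.
- Section 2.9 gives the DTxO arm "a cognitive–behavioural assessment and support program, alerts and reminders", plus chat and online visits.
- Section 2.11 says of the other arm: "Patients in the control group will be provided with a dietary plan and nutritional education and behavioral contents in paper format".

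The primary objective in the Introduction compares weight loss between the arms at 6 and 12 months.

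**The concern.** Both rules end participation in the study, not merely use of the app. The article describes no outcome collection after such an exit. Weight that is never measured cannot be recovered by any later analysis; it can only be modelled under assumptions.

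The psychopathology rule is the more serious of the two, for three reasons.

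- **Link to outcome.** A patient who does badly on the psychological measures is removed from their later measurement. A link to weight is inferred rather than stated, but distress and binge eating plausibly bear on weight.
- **Link to arm.** The experimental app delivers a cognitive-behavioural programme, while controls receive behavioural content on paper. The treatment aims at the domain that triggers exit, so equal exit rates cannot be presumed.
- **Timing.** Exit at V1 falls before the 6-month comparison, and exit at V1 to V3 falls before the 12-month comparison.

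The unblinding rule has the same structure, since its trigger is a safety or management event, but it should affect few patients.

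At stake are the comparability of the randomised groups in a trial that section 2.9 calls confirmatory, and later safety information on patients who had a safety concern or a psychological problem.

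**Working it through.** **1. The plan's own sample size (section 2.12.1).** Inputs: difference 1.5 kg, SD 3.5 kg, two-sided alpha 0.05, power 80%, drop-out 30%.

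n per arm = 2 × SD² × (1.960 + 0.842)² / difference² = 2 × 12.25 × 7.85 / 2.25 = 85.5, so 86 per arm and 172 in total. Inflated: 172 / (1 − 0.30) = 245.7, so 246.

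Both stated figures reproduce. The drop-out allowance restores numbers, not comparability, so it does not answer the concern.

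**2. Bias in the weight difference.** For one arm let p be the share forced out, S the mean weight change of stayers, and D the gap between leavers and stayers. The mean of all randomised patients is S + p × D, so stayers alone misstate it by p × D. If D is the same in both arms, the between-arm bias is

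bias = (p_DTxO − p_control) × D.

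The article gives neither p nor D, so the values below are assumptions.

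| Difference in exit share | D = 2 kg | D = 5 kg | Share of 1.5 kg |
|---|---|---|---|
| 2 points | 0.02 × 2 = 0.04 kg | 0.02 × 5 = 0.10 kg | 3% to 7% |
| 5 points | 0.05 × 2 = 0.10 kg | 0.05 × 5 = 0.25 kg | 7% to 17% |

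The direction depends on which arm loses more patients and on the sign of D. With equal exit shares and equal D the bias is zero.

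**3. Psychological scores.** This was simulated for one arm with no true change: 400,000 patients, baseline plus V1 to V4, within-patient correlation 0.5 or 0.7, and exit when a score exceeds 1.5 or 2.0 SD. Patients above the cut-off at baseline were excluded, in the spirit of the entry limits in section 2.4.2. The score at the detection visit was kept and only later visits were lost. Bias is the mean change in stayers minus the mean change in all patients.

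| Comparison | Exits that precede it | Share lost | Apparent improvement |
|---|---|---|---|
| 6 months (V2) | V1 | 1.6% to 5.2% | 0.003 to 0.010 SD |
| 12 months (V4) | V1 to V3 | 3.8% to 12.6% | 0.006 to 0.023 SD |

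These are single-arm shifts. The rule applies to both arms, so the between-arm effect is the difference between two such shifts. The figures depend on the baseline exclusion. Without it, this model (equal correlation between all visits) gives essentially no bias in mean change.

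**The case against.** The strongest reply has four parts.

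**Unblinding is a formal act.** In section 2.8 it means a code break decided and documented by the investigator for a safety or management need. A reader might infer that controls, holding a sparse app, will be unblinded most often and so leave most often. The text does not support this, because guessing one's arm is not a code break in that sense. Section 2.10.1 also says "The physician will explain to the patient how to download, access, and use the assigned App"; a physician who already knows the assigned app rarely needs a formal break. This part stands, and it makes the unblinding rule a minor companion.

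**The triggering score is not said to be discarded.** A reader might infer that the worst psychological values are deleted from the endpoints. Section 2.10.2 does not say so. The responses have been given by the time they are assessed, and only later visits are lost. Detection at V2 need not cost the 6-month visit, and detection at V4 need cost nothing. Dropping the V4 score as well would give 0.02 to 0.07 SD, but that counts a loss the rule does not state. This part stands.

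**A single-arm shift is not a trial bias.** A 10% exit share with a 2 to 4 kg gap moves one arm's mean by 0.2 to 0.4 kg. Setting that against the 1.5 kg between-arm target assumes that the other arm has no such exits. This part stands too, and the between-arm formula above is the right one.

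**The article condenses a fuller protocol.** Follow-up after discontinuation and the analysis sets may be set out there. It therefore cannot be said that safety follow-up will certainly be lost, or that the primary analysis will abandon the randomised groups. But the two rules are stated in the text at hand, and a site that follows them literally stops collecting data. The reply lowers the severity without removing the defect.

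**Conclusion.** The defect is real and worth correcting, at the level of should-fix. Two rules in the current text end study participation after randomisation, and the main one is triggered by the same kind of measure that the trial reports as secondary endpoints.

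The plausible effect on the weight comparison is modest: 3% to 17% of the target difference over the range examined. That rests on assumed exit imbalances, an assumed weight gap and the same gap in both arms. The effect on psychological scores is small even within one arm and depends on assumed cut-offs and correlations.

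That exit will differ by arm is inferred from the content of the interventions and is not stated anywhere. A larger claim, such as a heavily biased primary result, would need exit rates that the article does not give. The case for acting is that the loss cannot be undone once a patient has left, and that preventing it costs little.

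**What to change.** Reword the closing sentence of section 2.8 and the exit rule in section 2.10.2 so that neither event ends scheduled outcome collection:

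- At the remaining V1 to V4 visits, continue to record clinic weight and adverse events, and the questionnaires where the patient agrees.
- Record the reason and date of the event.
- Keep the patient in the randomised arm for the primary analysis.

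Specialist referral, and every decision on app use or care, stays as the protocol has it. If the full protocol already provides for this follow-up, the two sentences need only be brought into line with it.

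The cost is amendment wording. The visits are already scheduled and the sample size does not change. The small downside is that some patients will decline further visits, so some data will still be missing.
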